## Abstract

**Background:**

Screening for colorectal cancer (CRC) significantly reduces mortality associated with this disease. In Australia, the National Bowel Cancer Screening Program provides regular fecal occult blood tests (FOBT) for those aged 50 to 74 years, however, participation rates in the program have plateaued at 36%. Given low uptake in the National Bowel Cancer Screening Program, it is necessary to explore alternate methods to increase CRC screening rates. Primary care is a promising adjunct setting to test methods to increase CRC screening participation. Primary care guidelines support the recommendation and provision of CRC screening to primary care patients. Those in the National Bowel Cancer Screening Program target age range frequently present to their primary care provider.

**Objective:**

This study tests the effect that a multicomponent primary care–based intervention has on CRC screening uptake when compared to usual care.

**Methods:**

Primary care patients presenting for an appointment with their primary care provider complete a touchscreen survey to determine eligibility for the trial. Those aged 50 to 74 years, at average risk of CRC, with no history of CRC or inflammatory bowel disease, who have not had an FOBT in the past 2 years or a colonoscopy in the past 5 years are eligible to participate in the trial. Trial participants are randomized to the intervention or usual care group by day of attendance at the practice. The intervention consists of provision of an FOBT, printed information sheet, and primary care provider endorsement to complete the FOBT. The usual care group receives no additional care.

**Results:**

The primary outcome is completion of CRC screening 6 weeks after recruitment. The proportion of patients completing CRC screening will be compared between trial groups using a logistic regression model.

**Conclusions:**

CRC screening rates in Australia are suboptimal and interventions to increase screening participation are urgently required. This protocol describes the process of implementing a multicomponent intervention designed to increase CRC screening uptake in a primary care setting.

**Trial Registration:**

Australian New Zealand Clinical Trials Registry ACTRN12616001299493; https://anzctr.org.au/Trial/Registration/TrialReview.aspx?id=371136&isReview=true (Archived by WebCite at http://www.webcitation.org/6pL0VYIj6). Universal Trial Number U1111-1185-6120.

## Introduction

Globally, colorectal cancer (CRC) is the third most common cancer in men and the second most common cancer in women [1]. Overall, it is the fourth leading cause of cancer death [2]. Worldwide, 1.4 million people are diagnosed with CRC every year, and 694,000 die as a result [2]. In Australia, CRC is the second most diagnosed and second most common cause of cancer death [3]. In 2012, 14,958 Australians were diagnosed with CRC and in 2013, 4162 died as a result of CRC [3].

The effectiveness of CRC screening using a fecal occult blood test (FOBT) has been established in several large randomized controlled trials (RCTs) [4-7]. Biennial FOBT screening reduces mortality from CRC by 13% to 33% [4-8]. FOBT is an affordable, accessible form of screening that can be completed by an individual in the privacy of their own home. Studies in the United States [9] and Israel [10] have found that the majority of participants prefer FOBT compared to other screening methods such as colonoscopy. Participants report that they prefer FOBT because it is convenient, affordable, less time-consuming, less painful when compared to other screening modalities, and requires no bowel preparation [9-11]. In Australia, guidelines recommend biennial FOBT for people aged 50 years and above who are at average risk of CRC [12].

Given the benefits associated with CRC screening, many countries, including Australia, have implemented population-based screening programs [13]. Population-based screening programs can be defined as those that provide a simple test to detect early signs of disease to all individuals in a target group, usually defined by age [14]. In Australia, those aged 50 to 74 years are mailed an invitation and FOBT kit as part of the federally managed National Bowel Cancer Screening Program [13]. Briefly, the program mails individuals an immunochemical FOBT, instructions, and a reply paid envelope. Completed tests are sent to a central processing laboratory. A reminder letter is sent to those not returning a test within 8 weeks [13]. Invitees returning a completed FOBT are able to nominate their primary care provider to receive test results.

The impact of this and other population-based screening programs is dependent upon achieving high rates of initial uptake and repeat screening among invitees. However, the most recent National Bowel Cancer Screening Program monitoring report indicated that, of the 1.4 million people sent an FOBT in 2013-2014, only 36% returned a completed FOBT [13]. Given this, there is an urgent need to explore ways to improve engagement in CRC screening.

Primary care is a potential setting to increase CRC screening participation. Primary care providers have frequent contact with those in the target age group for CRC screening [15], and giving advice on preventive care is perceived by patients as a key part of the primary care provider’s role [16]. Primary care guidelines [17-19] recommend that providers play a role in promoting CRC screening by assessing risk based on family history and providing screening advice and test referral. Despite this, a large proportion of primary care patients in Australia have not been screened at the recommended interval [20]. This suggests that in Australia, as in other countries, CRC screening advice is not routinely delivered in the primary care setting [21-23]. This may be due to a range of factors including limited time within the consultation [24-26], perceived lack of patient interest in conversations about CRC screening [21], and cultural barriers [27].

Systematic reviews have identified strategies that are effective for increasing CRC screening uptake in the primary care setting [28-31]. Two reviews concluded that supplying patients with free FOBT when they attended an appointment with their physician resulted in an increase in CRC screening uptake by 15% to 42% when compared to usual care [29,30]. Further, RCTs that included paper-based information on CRC screening using an FOBT also significantly increased CRC screening in the intervention group when compared to those that included no paper-based information or usual care [32,33]. RCTs have found that primary care provider endorsement (ie, recommendation to take part in screening) as part of an organized screening program invitation is associated with increased CRC screening uptake when compared to standard invitations [34,35]. Most studies, however, have evaluated primary care provider endorsement in the context of mail-based interventions [31,36]. Face-to-face endorsement within the context of a primary care consultation may have greater impact on screening uptake. While reviews have identified a number of potentially effective primary care–based strategies for increasing CRC screening, the majority of studies using opportunistic strategies have taken place in the United States [30,36]. Given that the United States has a different health care system than Australia, it is unclear how generalizable these findings are to the Australian primary care setting.

Building upon current evidence, this study incorporates effective strategies to deliver a multicomponent intervention to increase CRC screening in the Australian primary care setting. The intervention comprises a novel combination of printed information on screening, the provision of a free point-of-care FOBT, and face-to-face primary care provider endorsement of screening.

## Methods

### Hypotheses

Our first hypothesis is that compared to usual care participants, those allocated to the intervention group will report a 20% higher rate of CRC screening uptake at 6-week follow-up. Our second hypothesis is that compared to usual care participants, those in the intervention group will show a greater increase in knowledge from baseline to follow-up.

**Figure 1 figure1:**
[figure not shown]
Flow of participants.

### Trial Design and Setting

This study is taking place in 5 primary care practices in New South Wales, Australia. A cluster RCT design is being used with consenting participants allocated to the intervention or usual care group depending on the day they attend the practice (see Figure 1).

### Practice Eligibility and Recruitment

A convenience sample of primary care clinics has been recruited for this study. To ensure adequate throughput of patients, eligible practices were required to have at least 2 full-time equivalent primary care providers. Primary care practice managers were sent an invitation and information statement via email. Nonresponding practices were followed up by telephone. Of 18 invited practices, 5 agreed to participate. Practice managers and primary care providers within each practice received an information statement and provided written informed consent.

### Randomization

Using a computer-generated randomization table with block sizes of 4, recruitment days are randomly allocated using a 1:1 ratio to intervention or usual care. Randomization by day rather than individual participant was selected to minimize potential for contamination between experimental groups. The allocation cannot be concealed from the research assistant conducting participant recruitment; however, these staff do not have access to the assignment schedule and are only made aware of allocation the day prior to attending the practice.

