### Procedure for Assessing Eligibility

A two-stage process determines trial eligibility. Initial patient eligibility screening begins when reception staff flag patients in the target age range to the research assistant, who invites patients in the waiting room to complete a touchscreen survey to assess trial eligibility, and if eligible, to take part in the trial. Patients are provided with an information statement and allowed time to ask any questions they may have about the trial. Those providing written consent complete a 10-minute touchscreen survey in the waiting room prior to their primary care appointment. Assistance to complete the touchscreen survey is provided by the research assistance as required. Study participants do not receive compensation for their time in the study.

Second-stage patient eligibility screening is performed during the touchscreen computer survey:

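### A single fixed block size of 4 for recruitment days makes up to a third of days deducible in advance and so weakens the day-before disclosure safeguard (minor)

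*Protocol article*

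**What the plan says.** The protocol article, Randomization, sets the rule: "Using a computer-generated randomization table with block sizes of 4, recruitment days are randomly allocated using a 1:1 ratio to intervention or usual care". The day is the unit for a stated reason: "Randomization by day rather than individual participant was selected to minimize potential for contamination between experimental groups".

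The same section concedes that the trial is open to the recruiter: "The allocation cannot be concealed from the research assistant conducting participant recruitment". It then gives one protection: "these staff do not have access to the assignment schedule and are only made aware of allocation the day prior to attending the practice".

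Under Procedure for Assessing Eligibility, that same role approaches patients: "reception staff flag patients in the target age range to the research assistant, who invites patients in the waiting room". Under Intervention, the research assistant hands the envelope to eligible participants on intervention days, so the arm of each past day is plain to whoever recruited on it.

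Trial Design and Setting gives the number of sites: "This study is taking place in 5 primary care practices in New South Wales, Australia". Analysis and Sample Size plans 80 participants per arm and assumes 10 eligible participants per day on average. Results reports 100 participants enrolled at submission.

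The article does not say whether there is one list or one per practice, whether recruiting staff were told the block size, or who sets the visit dates.

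**The concern.** The protection works only through lead time: staff are not meant to know a day's arm until the day before. With one fixed small block at 1:1, part of the sequence follows from its own past. The fourth day of a block is always settled by the first three, and the third is settled whenever the first two match. On those days the arm is known as soon as the preceding day's arm is disclosed, without sight of the list.

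Patients enter the trial through the day on which they attend. If whoever arranges visits knew an upcoming arm early, a visit could be placed, moved or skipped with that knowledge. The patients seen on intervention and usual care days could then differ before consent. Neither cluster-robust variance nor adjustment for site, both named in Analysis and Sample Size, corrects a difference of that kind.

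**Working it through.** **Inputs.** Block size 4 and ratio 1:1 (Randomization). 80 per arm, so 160 in all, and 10 eligible participants per day (Analysis and Sample Size). 5 practices (Trial Design and Setting). 100 enrolled (Results). The plan gives no figure for predictability, so there is none to reproduce.

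**Step 1: certain days in a complete block.** Two intervention and two usual care days can be ordered in 4!/(2!·2!) = 6 equally likely ways.

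| Day in block | Probability that the arm is certain from earlier days | Best-guess accuracy |
|---|---|---|
| 1 | 0 | 1/2 |
| 2 | 0 | 2/3 |
| 3 | 1/3 (days 1 and 2 match in 2 of 6 orders) | 2/3 |
| 4 | 1 | 1 |

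Expected certain days = 0 + 0 + 1/3 + 1 = 4/3 of 4, or 33.3%. Mean accuracy = (0.500 + 0.667 + 0.667 + 1.000)/4 = 70.8%, against 50% by chance.

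**Step 2: number of days.** 160/10 = 16 recruitment days. With one list whose every day is seen by the same observer, 16 × 1/3 = 5.3 days are certain in advance.

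**Step 3: if lists run by practice.** 16/5 = 3.2 days per practice, so most blocks are never completed. Over the first three days of a block, the certain share is (0 + 0 + 1/3)/3 = 1/9 = 11.1%. Complete blocks in one list give 33% and truncated practice-level blocks about 11%. The article does not say which applies.

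**Step 4: effect of varying the block size.** Simulated 16-day lists (20,000 replicates), with an observer who knows the set of possible sizes but not each draw:

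| Block sizes | Certain days | Best-guess accuracy |
|---|---|---|
| 4 only | 33% | 70.8% |
| 4 and 6 | 5.9% | 68.4% |
| 4, 6 and 8 | 2.4% | 66.9% |

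The change removes most of the certainty but little of the informed guessing.

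**Step 5: what is left to protect.** 160 − 100 = 60 participants, or 60/10 = 6 days. Under fixed blocks, 6 × 1/3 = about 2 of these days would be certain in advance.

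**The case against.** The strongest reply is that the larger exposure is already conceded and does not depend on the blocks. The research assistant knows the arm on every day before inviting anyone, so selective invitation is possible under any block size. This stands. Fixed blocks add only longer notice on some days, and no block scheme removes the rest.

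Second, the one-third figure needs an observer who knows the block size and boundaries and has seen every earlier day of one list. The article establishes none of this. Training of Staff speaks of research assistants in the plural, and with one overall list the staff of a single practice would see only part of it. This also stands, and it is why the result is given as up to one third.

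Third, a reader might infer that reception or booking staff could steer patients by arm. The documents do not support that. Flagging follows an age range, trial eligibility is set by the survey, and nothing shows that these staff know the block size or upcoming arms.

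Fourth, a reader might put a bias on the result. Suppose that steering shifts participants' baseline propensity to screen by ±e points according to the guessed arm. The arm difference then moves by 2 × (2 × 0.708 − 1) × e = 0.83e. But e has no basis in the documents. With sizes 4, 6 and 8 the multiplier is still 2 × (2 × 0.669 − 1) = 0.68, so most of any such bias would survive the change. It cannot be offered as the size of this problem.

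What remains is that the section states both a limit on lead time and a block rule that erodes it. That is a choice the article fixes, not a detail left to a fuller document.

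**Conclusion.** The point holds as a minor one. The fixed block of 4 works against the protocol's own safeguard: up to 33% of days can be deduced in advance, and about 11% if lists run by practice with about 3 days each. These figures assume an observer who knows the block size and boundaries and has seen every earlier day of the block. The numbers of days also rest on the plan's assumed 10 participants per day.

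It would be tempting to say that the safeguard fails. The figures do not support this, since even at the upper end two thirds of days stay uncertain until disclosure. Nor do the documents show that any selection of days took place; they show only an opportunity for it.

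**What to change.** For recruitment days not yet allocated:

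- Set the calendar of practice visits first, then draw the list, so that no visit is placed or moved once its arm can be guessed. This closes the day-choice route however well anyone guesses.
- Generate the list with randomly varying block sizes (for example 4, 6 and 8) that are not disclosed to research assistants or practices.
- Amend the statement of block size in Randomization, and report how many days were allocated under each scheme.

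**Cost.** One rerun of the list and one amended sentence through the amendment route described under Monitoring, with no extra patients. If recruitment ends mid-block, the arms may differ by up to 4 days with a largest block of 8 (8/2), against up to 2 days now (4/2). At 10 participants per day that is about 40 against 20 participants.

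**Limits.** The benefit reaches only the roughly 60 participants (about 6 days) outstanding at submission, and fewer if recruitment has moved on. The recruiter's knowledge of the arm at the moment of invitation is untouched.

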### Participant Eligibility Criteria

Those who (1) are aged 50 to 74 years, (2) have no personal history of bowel cancer or inflammatory bowel disease, (3) are at average risk of CRC, and (4) have not had an FOBT in the past 2 years or a colonoscopy in the past 5 years are eligible to participate in the trial.

### Exclusion Criteria

Those who are (1) not seeing a primary care provider, (2) too unwell, (3) unable to complete the touchscreen survey, or (4) unable to speak and read English sufficiently are excluded from the trial.

### Training of Staff

All training is delivered by one of the chief investigators prior to any recruitment. A training manual for research assistants developed by the research team is used for both training and as a reference during recruitment and follow-up. All research assistants receive face-to-face and on-site training in recruitment and data collection procedures. Reception staff are provided with an overview of the project as well as the process to identify eligible patients and how to refer them to the research assistant. A sign reminding reception staff to check patients for eligibility is placed at their workstation. One of the chief investigators attends a regular staff meeting at each practice to brief the primary care providers about the project and provide them with a dialogue sheet to encourage FOBT completion by patients assigned to the intervention group.

### Procedure for Assessing Eligibility

A two-stage process determines trial eligibility. Initial patient eligibility screening begins when reception staff flag patients in the target age range to the research assistant, who invites patients in the waiting room to complete a touchscreen survey to assess trial eligibility, and if eligible, to take part in the trial. Patients are provided with an information statement and allowed time to ask any questions they may have about the trial. Those providing written consent complete a 10-minute touchscreen survey in the waiting room prior to their primary care appointment. Assistance to complete the touchscreen survey is provided by the research assistance as required. Study participants do not receive compensation for their time in the study.

Second-stage patient eligibility screening is performed during the touchscreen computer survey:

No personal history of bowel disease: Participants are asked whether they have ever received a diagnosis of bowel cancer or inflammatory bowel disease (yes/no). FOBT screening recommendations related to biennial FOBT are only relevant to asymptomatic individuals with no prior history of CRC. Therefore, those who respond “yes” are excluded.Average risk for CRC: Participants are asked “How many of your first-degree relatives have ever been diagnosed with bowel cancer?” (0, 1, 2 or more) and “Were any of your relatives who have had bowel cancer diagnosed before the age of 55?” (yes/no). Based on criteria in the Australian National Health and Medical Research Council guidelines [12], those who report no relatives diagnosed with CRC aged younger than 55 years and up to one first-degree relative diagnosed with CRC at any age are classified as average risk for CRC. Those classified as at higher risk of CRC are excluded, as biennial FOBT recommendations do not apply to higher risk populations for whom more intensive methods of screening may be recommended. These participants receive a sealed envelope containing information about their survey results and are advised to discuss this with their primary care provider during their appointment.Overdue for CRC screening: Average risk participants are asked to report whether they have ever had an FOBT or colonoscopy and, if so, when they had their most recent test. National Health and Medical Research Council guidelines recommend that average risk persons in the eligible age range undergo FOBT every 2 years [12]. Colonoscopy is not recommended as a routine screening test in Australia for those at average risk [12] but may be undertaken for other reasons (eg, the investigation of symptoms). Therefore, only those who report that they have not had an FOBT in the past 2 years or colonoscopy in the past 5 years are eligible for the trial.

The survey end screen contains a code that indicates to the research assistant if the participant is eligible for the trial. Eligible participants then receive the intervention if they attend the practice on an intervention day.

### Intervention

Immediately after completing the touchscreen survey, those participants identified as eligible for the trial and attending the practice on an intervention day are provided with a large envelope by the research assistant and advised to take it into their appointment with the primary care provider. This contains an FOBT kit accompanied by a referral form, instructions and a postage paid envelope addressed to a commercial pathology laboratory and a printed information sheet. The information sheet is a single-page A4 sheet using bold colored boxes to separate the information. The information encompasses topics including the type of screening test they should complete and how often they should complete this, what to do with the FOBT, what a positive FOBT result means, and credible websites where further information about bowel cancer screening can be obtained. The information sheet has a Grade 8 Flesch-Kincaid reading level.

When the participant takes the envelope into their appointment, the primary care provider explains the importance of FOBT and encourages the participant to complete the test.

